#### Re-definition of primary endpoint

The primary outcome is a composite of three questions. The first question (Q1) assesses to what extent the participant’s pain has interfered with daily activities in the previous 6 months. This is assessed on a scale of 0 to 10, with higher scores indicating more interference. The last two questions assess to what extent the participant’s pain has changed their ability to (a) take part in recreational, social, and family activities (Q2); and (b) work (Q3). Both these questions are measured on a scale from 0 to 10, with higher scores indicating more extreme change.

For the last two questions, higher change scores are meant to represent a higher *negative* change. However, it is possible that some participants have misinterpreted this, and have recorded a high score to indicate a large positive change. We will therefore perform a sensitivity analysis by redefining the outcome for participants whose scores indicate they may have misinterpreted the intended direction of the questions relating to change.

For participants with a score of 2 or less for Q1 (indicating very little interference in daily activities) *and* a score of 8 or higher on either Q2 or Q3 (intending to indicate an extreme negative change in their ability to take part in social activities or to work), we will assume the participant has misinterpreted the intended direction of the scale for Q2 or Q3 (as it is inconsistent for the pain to have had very little interference in daily activities, and for there to have been an extreme negative change in the participant’s ability to take part in activities or work). We will therefore rescore Q2 or Q3 based on a reverse scale (that is, a score of 10 will be rescored as 0, 9 will be rescored as 1, and 8 will be rescored as 2). We will then re-analyse the outcome using the same method as for the main analysis.

### Subgroup analyses

Subgroup analyses will be performed for the primary outcome (CPG disability at 12 months). All subgroup analyses will be performed using the same analysis model as for the primary outcome, but will also include the subgroup of interest and a treatment-by-subgroup interaction. Interaction tests will be considered significant at the 5% level. No correction will be made for multiple tests.

The following subgroups will be assessed:

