**Figure 1 F1:**
[figure not shown]
**Schedule of assessment.** CPG, Chronic Pain Grade (Von Korff [3]); HADS, Hospital Anxiety and Depression Scale (Zigmond and Snaith [5]); EQ-5D, Quality of life (EuroQol.org); PSEQ, Pain Self-Efficacy Questionnaire (Nicholas 1989, [4]); CPAQ, Chronic Pain Acceptance Questionnaire (McCracken [6]); HEIQ, Social integration [7]; Census global health question (ons.gov.uk/census/2011-census).

**Table 1 T1:** The Coping with Persistent Pain, Effectiveness Research into Self-management (COPERS) course content overview

**Day (10.00 am to 2.45 pm)**	**Modules**
**Day 1**	Introduction and understanding pain and acceptance
Living and dealing with pain	
	Lunch
	Activity: Art
	Mind, mood and pain
	Movement and posture, and Relaxation
**Day 2**	Dealing with unhelpful, negative thoughts and barriers to change
Doing something about your life with pain	
	Lunch
	Activity: Hand massage
	Making pain more manageable
	Movement and Relaxation
**Day 3**	Communication skills
Communication and relationships	Lunch
	Activity: Volunteering
	Movement and Relaxation
**Day 4**	The future
Follow-up (2 weeks later, 10.00 am to 12.00)	

The original sample size calculation called for 685 participants (391 in the intervention group and 294 in the control group, to be randomised in a 4:3 ratio). However, we required a sufficient number of participants in each group-based learning course to make the intervention viable; therefore, we continued recruitment until there was an adequate number of participants for each course. This led to 703 participants (403 intervention, 300 control).

Ethics approval was granted by Cambridgeshire Ethics 11/EE/04. All patients provided written informed consent prior to randomisation.

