### Analysis principles

#### General analysis principles

The main analysis for each outcome will use intention-to-treat (ITT) principles, meaning that all participants with a recorded outcome will be included in the analysis, and will be analysed according to the treatment group to which they were randomised [10]. More information on which participants will be included in each analysis is available in later sections. All *P* values will be two sided, and the significance level is set at 5%.

Analyses for all outcomes will be presented as:

1. The number of participants included in the analysis, by treatment group;

2. A summary measure of the outcome, by treatment group (for example, mean (SD) for continuous outcomes, number (%) for binary outcomes). Only participants with a completely recorded outcome will be used to calculate the summary measure (for example, participants who complete only one of three components of the CPG disability score will not be included in the calculation of the summary measure, although they will be included in estimated the treatment through the use of multiple imputation - see later sections);

3. A treatment effect, with a 95% confidence interval;

4. A two-sided *P* value.

All analyses will account for clustering by course in the intervention group. This is because when the intervention is delivered in clusters (for example, in a group setting, or when the same therapist treats multiple patients) it is necessary to account for the clustering in the analysis to avoid increasing the type I error rate [11-13]. Participants in the control group (who do not attend courses), will act as their own cluster (that is, each participant in the control group will belong to a 'course’ where they are the only member).

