### Analysis of primary outcome

The primary outcome (CPG disability at 12 months) will be analysed using a mixed-effects linear regression model, with a 'group-based learning course’ as a random effect. Restricted maximum likelihood (REML) will be used. The model will include site of recruitment, age, gender, HADS depression score, and CPG disability at baseline as covariates.

All participants who completed at least one of the three questions that form the CPG disability score at either 6 or 12 months will be included in the analysis. Participants who did not fill out any portion of the CPG disability score at both 6 or 12 months will be excluded from the analysis.

Multiple imputation (MI) [28] will be used to account for participants who have an observed outcome at 6 months, but are missing the outcome at 12 months, as well as for participants who completed some, but not all, of the questions on the CPG disability score at 12 months. A total of 20 imputations will be performed, and results will be combined using Rubin’s Rules [28]. Only participants included in the analysis will be included in the imputation model. The imputation model will include the three questions that form the CPG disability score at baseline, 6 months, and 12 months, as well as the site of recruitment, age, gender, the HADS depression score at baseline, and employment status (employed or in full-time education versus not employed or in full-time education) (14 variables in total). We chose to include these variables in the imputation model because they will be included in the analysis model (CPG disability score at baseline, 6 months, and 12 months, site of recruitment, age, gender, and HADS depression score at baseline) or because we felt they may be predictive of missingness (employed or in full-time education versus not employed or in full-time education). Imputation will be performed separately within each treatment group [29]. In the intervention group, multilevel imputation will be performed, with 'course’ included in the imputation model as a random effect [30,31].

Missing data in any of the covariates to be adjusted for in the analysis (site of recruitment, age, gender, HADS depression score, CPG disability and baseline) will be accounted for at the same time as missing data in the CPG disability score at 6 or 12 months, as these variables will be included in the same imputation model.

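### Six of the eight subgroup variables are not in the imputation model, so their treatment-by-subgroup interactions will tend to be modestly attenuated

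*SAP article*

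**What the plan says.** Under Analysis of primary outcome, the imputation model is listed in full: the three CPG disability items at baseline, 6 and 12 months, plus site, age, gender, baseline HADS depression and employment status ("14 variables in total"). The reason given is "We chose to include these variables in the imputation model because they will be included in the analysis model" or, for employment, that it may predict missingness. Imputation is done separately in each arm. It covers only participants who answered at least one CPG disability item at 6 or 12 months; the rest are excluded.

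Under Subgroup analyses, the plan says "All subgroup analyses will be performed using the same analysis model as for the primary outcome". That model is extended by a main effect for the subgroup and by its product with treatment. Eight subgroup variables follow, four headed Non-pain and four headed Pain-related. On testing, the plan says "Interaction tests will be considered significant at the 5% level" and "No correction will be made for multiple tests". The section does not mention imputation, and it gives no rule for a missing subgroup value.

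**The concern.** An imputation model should contain every term whose effect the analysis model estimates. Imputing by arm preserves treatment-by-covariate interactions, but only for covariates that are in the imputation model. For six of the eight subgroup analyses the key covariate is not there. The 12-month scores filled in for those analyses are drawn as if, given the model's other variables, the subgroup made no further difference in either arm. Mixing them with observed scores pulls the estimated interaction away from its true value, usually towards zero.

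At stake are six secondary interaction tests, which could understate real differences between subgroups and lose some power. The planned missing-data sensitivity analyses concern the overall treatment effect, so they would not reveal this.

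**Working it through.** **Reproducing the plan's count.** Three items at three times give 9 variables. Site, age, gender, HADS depression and employment add 5. 9 + 5 = 14, as stated.

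**Cross-check against the subgroup list.** Two variables are present: baseline disability (as its three items) and baseline depression (as the HADS score). Six are absent: comorbidity, living arrangements, PSEQ, deprivation, pain duration and baseline CPG intensity.

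**Size, by formula.** Let f be the share of analysed participants whose 12-month score is imputed, b the slope of the 12-month on the 6-month score within arm, and θ6 and θ12 the interactions at the two times. Observed scores contribute θ12. Imputed scores contribute about bθ6. So

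share of the interaction retained = (1 − f) + f × b × (θ6/θ12).

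The document gives none of these inputs, so ranges are assumed:

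| f | b = 0.4, θ6 = θ12 | b = 0.6, θ6 = θ12 | b = 0.8, θ6 = θ12 | θ6 = 0 |
|---|---|---|---|---|
| 5% | 0.97 | 0.98 | 0.99 | 0.95 |
| 10% | 0.94 | 0.96 | 0.98 | 0.90 |
| 20% | 0.88 | 0.92 | 0.96 | 0.80 |

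For example, 0.80 + 0.20 × 0.4 = 0.88. With θ6 = 1.5 × θ12, b = 0.8 and f = 20%, the share is 0.80 + 0.20 × 0.8 × 1.5 = 1.04, so the interaction is slightly inflated.

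**Size, by simulation.** The arms were 403 and 300, as randomised (SAP article, Background). Imputation was by arm, with 20 imputations and Rubin's rules, as planned. Assumed: one binary subgroup split 50:50, residual SD 20, true 12-month interaction 10 points, and scores missing completely at random. Simplified: total scores instead of items, and no course effect. There were 1,000 runs per setting (2,000 when the true 12-month interaction was zero). The Monte Carlo SE was about 0.1 or less.

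- Equal interactions, subgroup variable omitted, correlations 0.4, 0.6 and 0.8: mean estimates 9.81, 9.82 and 9.87 at f = 5%; 9.38, 9.69 and 9.72 at f = 10%; 8.86, 9.18 and 9.60 at f = 20%. These agree with the formula.
- Same settings, subgroup variable included: 9.8 to 10.2 throughout.
- No 6-month interaction, f = 10%, correlation 0.6: 8.9, with power 81% against 87% for complete cases.
- 6-month interaction of 20, same f and correlation: 10.2, no attenuation.
- No 12-month interaction but a 6-month one of 10, same f and correlation: 0.58, away from zero (formula: 0.10 × 0.6 × 10 = 0.6).
- No interaction at either time: no detectable bias, and type I error 4.4%.

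**Power at the unfavourable end** (f = 20%, correlation 0.4, equal interactions). Power was 78% without the variable and 84% with it. The two came from separate draws, in which complete-case power was 81.6% and 84.5%, so part of the 6-point gap is Monte Carlo error.

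**Scale.** With full data the SE of the interaction is √[400 × (2/201.5 + 2/150)] = √9.30 = 3.05. A loss of 12% of 10 points is 1.2 points, or 0.39 SE. A loss of 4% is 0.4 points, or 0.13 SE.

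**The case against.** The strongest reply is that the fault is read from silence. The article is condensed and distinguishes the analysis model from the imputation model. It states reuse of the primary imputed datasets only for the adherence-adjusted analysis. Applied consistently, the plan's own reason for choosing imputation variables would bring each subgroup variable in.

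This stands only in part. The article says how imputation changes wherever it intends a change: the first missing-data sensitivity analysis, PSEQ, CPAQ, EQ-5D and the census question. For subgroups it states none, so the natural reading is that the 14-variable model is used unchanged.

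The reply is right about size. The effect is small unless many scores are imputed, only secondary tests are touched, and false-positive control is intact when there is no interaction at either time.

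A reader might also infer three stronger points, which the document does not support:

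- **That imputed scores carry no subgroup effect.** Everyone imputed has at least one item at 6 or 12 months. The arm-specific model passes on part of any effect through those answers.
- **That the tests are certain to be biased towards no difference.** The direction depends on the unknown 6-month interaction and can vanish or reverse.
- **That participants missing a subgroup value will be dropped.** The plan does not say so. It states no rule for these values, while elsewhere it fills in missing baseline covariates.

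**Conclusion.** The point holds in a limited form. As written, the imputation model does not match six of the eight interaction models and departs from the plan's own stated reason for choosing its variables. Interactions that persist from 6 to 12 months will tend to be attenuated: by about 1% to 12% for 5% to 20% imputed and a slope of 0.4 to 0.8 if equal at both times, and by up to the imputed share if absent at 6 months. Partly answered 12-month scores, which were not simulated, would carry more of the effect through their observed items.

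All sizes rest on assumed imputed shares, correlations and interactions. They also rest on missingness completely at random and on no course effect. The primary treatment effect is not affected.

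**What to change.** Add a sentence under Subgroup analyses: where the subgroup variable is not already in the primary imputation model, the imputation is repeated separately in each arm with that variable added, in the form used in the analysis. One variable per analysis keeps the multilevel model in the intervention arm small; the plan itself is wary of large imputation models under CPAQ. Imputing by arm then preserves the treatment-by-subgroup interaction, and the same step handles missing subgroup values.

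The cost is six further imputation runs with slightly larger models. PSEQ, pain duration and CPG intensity have three levels, so each needs two indicator terms and, where values are missing, an imputation method suited to categories.

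A complete-case interaction check would be a weaker substitute. It was unbiased in the simulation because missingness was completely at random, which cannot be assumed in the trial.

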#### Non-pain

•Comorbidity (number of body systems affected): ≤3 versus >3 comorbidities (with chronic musculoskeletal pain counting as a comorbidity)

•Living arrangements: living alone versus living with others

•Baseline self-efficacy: PSEQ score 0 to 20 (not likely to be confident) versus 21 to 39 (more likely to be confident and to self manage) versus ≥40 (confident)

•Socioeconomic status (SES) (based on the Index of Multiple Deprivation 2010, calculated from participant postcodes via Geographical Information Systems (GIS): lower social class (less than observed median in data) versus higher social class (equal or greater than observed median in data)

#### Pain-related

•Pain duration: 0 to 12 months versus 13 months to 4 years versus 5 or more years

•Baseline pain intensity: CPG intensity score 0 to 3 (low) versus 4 to 7 (medium) versus 8 to 10 (high)

•Baseline pain-related disability: CPG disability score 0 to 3 (low) versus 4 to 7 (medium) versus 8 to 10 (high)

•Baseline depression: HADS depression score <11 versus ≥11

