### Outcomes

#### Primary outcome

The primary outcome was the pain-related disability score (which is a subscale of the Chronic Pain Grade questionnaire (CPG disability) [3]) at 12 months post-randomisation.

The three questions in this subscale assess the extent to which the participant’s pain has, in the previous 6 months: (i) interfered with their ability to perform their daily activities; (ii) changed their ability to take part in recreational, social, and family activities; and (iii) changed their ability to work. Each of the three questions is rated on a scale of 0 to 10, with 0 reflecting no change or interference, and 10 reflecting extreme change or interference.

The primary outcome is the mean of these three questions, multiplied by 10; that is, if X1, *X*2, and X3 represent the three questions, and Y represents the primary outcome, then:

$$Y=10*\left(X1+X2+X3\right)/3$$

The primary outcome is therefore recorded on a scale from 0 to 100, with higher scores reflecting larger interference or change in the participant’s ability to perform daily activities, work, or take part in recreational, social, and family activities.

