#### Secondary outcomes

The secondary outcomes are:

1. CPG disability at 6 months post-randomisation [3]

2. CPG pain intensity score at 6 and 12 months post-randomisation [3]

3. Pain Self-Efficacy Questionnaire (PSEQ) score at 6 and 12 months post-randomisation [4]

4. Hospital Anxiety and Depression Scale (HADS) Anxiety score at 6 and 12 months post-randomisation [5]

5. Hospital Anxiety and Depression Scale (HADS) Depression score at 6 and 12 months post-randomisation [5]

6. Chronic Pain Acceptance Questionnaire (CPAQ) score at 6 and 12 months post-randomisation [6]

7. Health Education Impact Questionnaire (HEIQ) Social integration score at 6 and 12 months post-randomisation [7]

8. EQ-5D at 6 and 12 months post-randomisation [8]

9. Census global health question at 6 and 12 months post-randomisation [9]

10. Total Defined Daily Doses (Total DDD) of psychotropic drugs consumed up to 12 months post-randomisation

11. Total DDD of analgesics (including all opioids and other central nervous system drugs) consumed for pain up to 12 months post-randomisation

12. Total DDD of weak opioids consumed up to 12 months post-randomisation

13. Total DDD of strong opioids consumed up to 12 months post-randomisation

14. Proportion of participants using weak opioids at 12 months post-randomisation (defined as having received a prescription for a weak opioid up to twelve weeks before the 12-month follow-up date)

15. Proportion of participants using strong opioids at 12 months post-randomisation (defined as having received a prescription for a strong opioid up to twelve weeks before the 12-month follow-up date)

A guide to how outcomes are derived is available in Additional file 1.

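### The baseline CPG disability subgroup bands run from 0 to 10, but the plan defines the score on 0 to 100, and the bands miss attainable values on either scale

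*SAP article*

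**What the plan says.** In the SAP article, the Primary outcome section gives the full derivation of the CPG disability score. "Each of the three questions is rated on a scale of 0 to 10", and "The primary outcome is the mean of these three questions, multiplied by 10". The section then gives the resulting range: "The primary outcome is therefore recorded on a scale from 0 to 100". The section on participants with no completed follow-ups works on the same scale, with assumed control-group means from 10 to 90.

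The Pain-related list under Subgroup analyses uses the same named score with different numbers: "Baseline pain-related disability: CPG disability score 0 to 3 (low) versus 4 to 7 (medium) versus 8 to 10 (high". The line above it gives identical cut-points for pain intensity: "CPG intensity score 0 to 3 (low) versus 4 to 7 (medium) versus 8 to 10 (high". Neither line mentions rescaling or rounding.

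For each subgroup, the Subgroup analyses section adds the subgroup and its interaction with treatment to the primary model and tests the interaction at 5%, without adjusting for the number of tests.

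The text shown does not state the scale of the intensity score. The Secondary outcomes section says only: "A guide to how outcomes are derived is available in Additional file 1". That file is not at hand.

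**The concern.** The three disability bands stop at 10, and the score they are meant to divide goes up to 100. Read as written, the group labelled high sits near the bottom of the scale, and every score above 10 belongs to no group.

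The bands are also written as whole-number ranges (3 then 4, 7 then 8), while an average of three whole-number items moves in thirds. Correcting the scale therefore leaves some attainable values without a group.

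At stake is the prespecified test of whether the treatment effect depends on the baseline level of the primary outcome. To run it on everyone, the analyst must make a choice that the plan does not record. The General analysis principles warn against choosing methods on the basis of trial data because of bias and loss of type I error control. An explicit banding rule meets that aim here.

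**Working it through.** **Inputs.** Three items, each 0 to 10; score Y = 10 × (X1 + X2 + X3) / 3 (Primary outcome section). Bands 0 to 3, 4 to 7 and 8 to 10 (Pain-related list).

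**The plan's own range.** With whole-number items, the sum s = X1 + X2 + X3 runs from 0 to 30, so Y = 10s/3 runs from 0 to 10 × 30/3 = 100. This reproduces the stated range. There are 31 attainable scores, in steps of 3.33.

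**Reading A: bands applied to the 0 to 100 score.**
- s = 0 gives 0: low.
- s = 1 gives 3.33: between bands.
- s = 2 gives 6.67: medium.
- s = 3 gives 10: high.
- s = 4 to 30 give 13.33 to 100: above every band (27 values).

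Classified: 3 of 31. Unclassified: 27 + 1 = 28 of 31. Of these 28, 27 are due to the scale and one to a gap.

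**Reading B: bands applied to the 0 to 10 item mean, s/3.**
- s = 10 and 11 give 3.33 and 3.67: between low and medium.
- s = 22 and 23 give 7.33 and 7.67: between medium and high.
- All other values fall in a band.

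Unclassified: 4 of 31. On the 0 to 100 scale these are 33.3, 36.7, 73.3 and 76.7. In item combinations they account for 66 + 75 + 45 + 36 = 222 of 11³ = 1,331, or 16.7%. That figure weights all combinations equally and is not an estimate for the trial population.

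**Illustration under assumptions.** The article gives no baseline mean or SD. Assuming a discretised normal distribution with mean 30 to 70 and SD 15 to 30 on the 0 to 100 scale, Reading B leaves about 12% to 18% unclassified, or about 82 to 126 of the 703 randomised. These inputs are assumptions.

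**Does the unstated choice matter?** Rounding the item mean to the nearest whole number puts 3.33 in low, 3.67 and 7.33 in medium, and 7.67 in high. Truncating puts 3.67 in low and 7.67 in medium. The two conventions disagree on two of the four values, so group membership depends on which is used.

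**Imputed data.** The primary imputation model includes the three baseline items. The article does not say whether imputed items are kept to whole numbers. If they are not, further values could fall between 3 and 4 or between 7 and 8.

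**Check of the example cuts.** With below 35, 35 to below 75, and 75 or above: 33.3 is low, 36.7 and 73.3 are medium, and 76.7 is high. All 31 values are classified, exactly as by rounding the item mean.

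**The case against.** The best defence is that no analyst would follow Reading A. The bands end at 10, match the item scale and are labelled low, medium and high, so the item mean before multiplication by 10 is the natural intention. Rounding to a whole number then classifies everyone. Banding uses baseline values only and needs no treatment codes. What is missing would then be a note on scale and rounding.

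Much of this stands. A reader might infer from the literal count that most participants fall in no subgroup. The document does not support that as a practical claim: it holds only under Reading A, where the cause is the scale and not the gaps. Under the likely intention a minority is affected, and its size is unknown. It would also be too strong to say that new cut-points must be chosen after unblinding, since the open choice concerns a scale and, for whole-number items, four score values.

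Two other extensions are tempting and do not hold:
- **Intensity.** The cut-points are the same, but the text shown gives no range for that score, so a 0 to 100 mismatch is not established. The gaps matter there only if the score can take values between whole numbers.
- **Pain duration.** The bands "0 to 12 months versus 13 months to 4 years versus 5 or more years" leave a gap only if duration was recorded finely enough to fall between 4 and 5 years. The recording format is not stated.

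The defence does not remove the contradiction. The article derives the disability score in full, then bands the same named score on another scale, and the charitable reading still needs a rule that is not written down. The HADS depression subgroup, split below 11 against 11 or more, shows that the plan can state contiguous bands.

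**Conclusion.** The point holds for baseline CPG disability. The bands contradict the score's definition: taken literally, 28 of 31 attainable scores have no group and 10 out of 100 is called high. On the probable 0 to 10 reading, 4 of 31 values remain unassigned. These counts rest only on the stated formula and whole-number items. The share of participants cannot be derived from the document; the 12% to 18% shown depends on assumed baseline distributions.

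For CPG intensity the point is conditional on that score also being an item average.

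This is a should-fix point. It concerns one of eight subgroup analyses for certain and possibly a second. Baseline disability enters the primary model as a continuous covariate, so the primary analysis does not use these bands and its estimate and P value are unaffected.

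**What to change.** State the scale on which baseline CPG disability is banded and make the bands contiguous. One option is below 35, 35 to below 75, and 75 or above on 0 to 100, which equals rounding the 0 to 10 item mean. Other contiguous cuts serve equally well if the sponsor intended them. The cuts should be set without reference to outcomes by treatment group.

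Use the same contiguous form for the CPG intensity bands if that score is an item average, and state its scale beside them. Contiguous bands also cover any non-integer imputed baseline values.

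The cost is a line or two of wording, with no new data and no change to the model. The article reports that follow-up is complete, so if the analysis has already been run, report the banding rule that was used and say when it was chosen.

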Site of recruitment (London or Midlands) [14-17], age, gender, and the HADS depression score at baseline will be included as covariates in each analysis [17-20]. Additionally, for continuous outcomes (CPG disability, CPG pain intensity, PSEQ, HADS Anxiety, HADS Depression, CPAQ, HEIQ, and EQ-5D), the outcome measured at baseline will be included in the analysis [19]. Site of recruitment will be adjusted for because it was used as a stratification factor in the randomisation process, and therefore, it is necessary to include it in the analysis to maintain correct type I error rates [11,14-16]. The other covariates will be included in the analysis because adjustment for prognostic factors can substantially increase power [17-21].

Continuous covariates (age, HADS depression score, outcome measured at baseline) will be analysed using a linear relationship with the outcome, as categorising continuous covariates has been shown to lead to poor performance in other scenarios [22]. We made the decision to assume a linear relationship prior to examining the observed association between covariate and outcome in the trial data, as previous research has shown that choosing the analysis method based on study data can lead to biased treatment effect estimates and incorrect type I error rates in some scenarios [23-27].

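### The subgroup interaction tests band continuous or count modifiers and do not carry over the plan's own reasoning against categorising; under stated assumptions this costs appreciable power

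*SAP article*

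**What the plan says.** Under General analysis principles, the SAP article states: "Continuous covariates (age, HADS depression score, outcome measured at baseline) will be analysed using a linear relationship with the outcome". Its reason is that "categorising continuous covariates has been shown to lead to poor performance in other scenarios".

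Under Subgroup analyses, each model is the primary model, "but will also include the subgroup of interest and a treatment-by-subgroup interaction". The decision rule is: "Interaction tests will be considered significant at the 5% level. No correction will be made for multiple tests".

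The modifiers at issue are defined in the Non-pain and Pain-related lists:

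- **Two bands:** HADS depression ("HADS depression score <11 versus ≥11"), comorbidity ("≤3 versus >3 comorbidities") and deprivation ("lower social class (less than observed median in data) versus higher social class (equal or greater than observed median in data").
- **Three bands:** PSEQ (0-20, 21-39, 40 or more), and CPG intensity and CPG disability (each 0-3, 4-7, 8-10).

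No interaction with any of these measures on its original scale is planned. Living arrangements is a natural two-category factor and raises no question. Pain duration is also in three bands, but the article does not say whether it was recorded more finely, so it is left out here.

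**The concern.** The argument for keeping continuous covariates linear is that cutting them up performs poorly. That argument applies at least as well to the modifier in an interaction test, yet the subgroup section cuts six such measures. The mismatch is most direct for HADS depression and baseline CPG disability. Because the subgroup model is the primary model plus extra terms, each of these scores enters once as a linear covariate and again in bands as the modifier.

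What is at stake is power. Interaction tests are usually the least powered tests in a trial, and here they are read against a 5% threshold. Information that was collected but not used makes a null subgroup result harder to interpret. A second, smaller matter is the deprivation split. It falls at the sample median, so the meaning of its two groups is tied to this sample.

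**Working it through.** The article gives no power, effect size or information figure for the interaction tests, so there is no stated value to reproduce.

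**Inputs from the article:** two-sided alpha of 5%; two bands (1 df) or three bands (2 df); 703 participants, 403 intervention and 300 control.

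**Assumptions, not in the article:** a normally distributed modifier, a linear interaction, and the band shares listed below.

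**Information kept.** This is the share of the modifier's variance explained by band membership.

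- Two bands cut at quantile p: φ(z_p)² / [p(1−p)]. At the median: 0.3989² / 0.25 = 0.637 (that is, 2/π). At 70/30: 0.3477² / 0.21 = 0.576.
- Three bands: Σ p_j m_j², where m_j is the mean of the modifier in band j. For equal thirds the outer means are ±1.091 and the middle mean is 0, so (2/3) × 1.091² = 0.793.

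**Power.** A continuous interaction with 80% power has noncentrality (1.960 + 0.842)² = 7.85. Banding multiplies this by the information kept. For two bands, power = Φ(2.80 × √kept − 1.96). At the median this is Φ(2.80 × 0.798 − 1.96) = Φ(0.275) = 0.61.

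**Cost of the second degree of freedom.** A 2-df test needs noncentrality of about 9.63 for 80% power, so three bands carry a further factor of 7.85 / 9.63 = 0.815. For equal thirds: 0.793 × 0.815 = 0.646, an equivalent loss of 35.4%.

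| Band shares (%) | Information lost | Loss counting df | Power (80% if continuous) |
|---|---|---|---|
| 50/50 | 36.3% | 36.3% | 61% |
| 60/40 | 37.8% | 37.8% | 60% |
| 70/30 | 42.4% | 42.4% | 57% |
| 80/20 | 51.0% | 51.0% | 50% |
| 90/10 | 65.8% | 65.8% | 37% |
| 27/46/27 (best three-band split) | 19.0% | 34.0% | 61% |
| equal thirds | 20.7% | 35.4% | 60% |
| 10/50/40 | 23.0% | 37.3% | 59% |
| 10/30/60 | 29.5% | 42.6% | 55% |
| 10/10/80 | 48.5% | 58.0% | 42% |

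The median is the best two-band cut for a normal modifier, so 36% is a floor for two bands. In sample-size terms, 703 × 0.637 ≈ 448 participants for that test.

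**Check by simulation.** With 4,000 trials at 403:300 and the linear main effect kept in the model, power was 78% for the continuous interaction, 60% for a median split, 55% at 70/30, 49% at 80/20, 59% for thirds and 57% at 10/50/40. This agrees with the table.

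**Sensitivity to the assumptions.** For a uniform modifier, k equal bands keep 1 − 1/k² of the information. The loss is then 1/4 = 25% for two bands and 1/9 = 11% for three, before the 2-df cost. If the treatment effect truly changes in a step at the chosen cut, banding loses nothing.

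**The case against.** Several points on the other side are sound.

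- **A breach of the plan's own rule?** A reader might infer one. The text does not support it: the statement on linearity concerns adjustment covariates, and its reason is qualified as coming from other scenarios. In the subgroup models HADS depression and baseline CPG disability do stay linear as covariates, so the statement is followed as written. What remains is reasoning that was not carried over to the modifiers.
- **A third or more lost everywhere?** Only the two-band cuts lose that much information, and only under normality and a linear interaction. Three bands lose less than a third for ordinary splits. They pass a third only when the 2-df test is counted or one band dominates. Normality is doubtful for a count of body systems.
- **Deprivation split left open?** It is not. The rule is fully prespecified, including ties, and the median of a baseline measure uses no outcome or treatment data. Only the cut value depends on the sample, which limits comparison with other trials.
- **Validity.** Prespecified bands do not bias the test or inflate its type I error, and the PSEQ bands carry stated meanings. These are subgroup analyses, so the primary estimate is untouched.

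These points limit the criticism to efficiency and consistency of reasoning. They do not remove it. The article claims no threshold effect at any of the cuts, and the clinical categories can still be displayed when the test itself is continuous.

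**Conclusion.** The point holds as an avoidable loss of power and an inconsistency of reasoning, clearest for HADS depression and baseline CPG disability. It is not an error that invalidates an analysis. With a roughly normal modifier and a linear interaction:

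- a two-band cut loses at least 36% of the information, and 80% power falls to about 61% or less;
- a three-band cut loses about 19-30% for ordinary splits, equivalent to about 34-43% with the 2-df test, and power falls to about 55-61%.

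Neither the distributions nor the band shares are in the documents, so these are ranges under assumption. The loss is smaller for a uniform modifier and absent for a true threshold at the cut. The change is worth making, in proportion to the place of subgroup analyses in the trial.

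**What to change.** For HADS depression, CPG disability, CPG intensity, PSEQ, deprivation and comorbidity count, prespecify the interaction test as treatment × continuous modifier (1 df), with the modifier's linear main effect in the model. Use the bands only to display effects by subgroup. A continuous deprivation term also removes the dependence of the test on the sample median. Living arrangements needs no change.

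Before the bands are used even for display, reconcile the CPG limits with the score. The Primary outcome section puts CPG disability on 0-100, whereas the bands run 0-3, 4-7 and 8-10. Even on a 0-10 mean of three items, values such as 10/3 = 3.33 or 23/3 = 7.67 fall between bands.

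The cost is a change of SAP wording, with no new data. The downside is the assumption of a linear interaction. A linear main effect is already in the primary model for only two of the six modifiers, HADS depression and baseline CPG disability. For PSEQ, CPG intensity, deprivation and comorbidity the fix adds linear main effects that the primary model does not contain.
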